### Sample size

A priori sample-size estimation is conducted to determine the number of participants required to detect the expected effects of the VR-based exposure intervention on the primary outcome measures. Evidence from a systematic review [21], which examined virtual reality–based interventions targeting public-speaking anxiety in student populations, indicates that VR exposure procedures typically yield moderate-to-large reductions in anxiety symptoms compared with control or baseline conditions. Reported effects across the studies reviewed are consistent with the magnitude commonly observed in the broader VRET literature, supporting the assumption of a moderately large effect size for the planned between-group comparison.

Based on this evidence, we adopt an expected effect size of Cohen’s d = 0.75 for the between-group differences in change scores from baseline to post-intervention between the VR exposure and control groups. A power analysis conducted using G*Power 3.1 (two-tailed independent-measures t-test, α = 0.05, power = 0.80) indicated that 29 participants per group would be required to detect an effect of this magnitude.

To ensure adequate statistical power after accounting for participant attrition, commonly estimated at 15%-20% in VR-based intervention studies, we plan for an upper-bound dropout rate of 20%. Accordingly, the required number of participants is adjusted to 36 participants per group, resulting in a total target sample of 72 participants [22]. This sample size is expected to provide sufficient statistical sensitivity to detect clinically meaningful effects of the VR intervention while remaining feasible for a single-site randomized controlled trial.

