### Statistical analyses

All statistical analyses are conducted using IBM SPSS Statistics (version 29.0) and follow a pre-specified analytic strategy designed to evaluate changes in psychological and physiological outcomes across the study period and to compare the effectiveness of standard counseling with and without VR-based exposure. Descriptive statistics are first computed to characterize the sample to assess baseline equivalence between groups. Reliability analyses (Cronbach’s α and McDonald’s ω) are performed to confirm the internal consistency of the psychometric instruments.

Because the study involves repeated assessments at baseline (T0), post-intervention (T1), and follow-up (T2), the primary analyses use linear mixed-effects models, an approach well suited to handling longitudinal data and missing observations. These models test for the main effects of time and group, as well as the critical time × group interaction, indicating differential improvement between the VR-enhanced counseling condition and the control group. Where significant interactions emerge, post hoc comparisons with Bonferroni adjustment are conducted to identify specific temporal patterns of change. Complementary analyses of change scores (ΔT1–T0 and ΔT2–T0) are performed using independent-sample t-tests or, where assumptions are violated, Mann–Whitney U tests; General Linear Models including baseline variables and demographic covariates further clarify group differences in treatment response.

Physiological data collected during VR sessions (including heart rate, HRV, and electrodermal activity) are examined through mixed models and event-based analyses aligned with the structure of the VR exposure tasks, allowing evaluation of both arousal patterns and recovery processes. Exploratory regression models are used to identify predictors of treatment benefit, such as baseline symptom severity or physiological reactivity during VR exposure.

Missing data are handled through the mixed-model framework, which accommodates incomplete longitudinal data; if dropout shows non-random patterns, multiple imputation is applied as a sensitivity check. For all analyses, statistical significance is set at α = 0.05, with appropriate corrections for multiple comparisons.

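### The planned multiple-imputation check shares the mixed model's missing-at-random assumption, so agreement between the two says little about dropout that depends on unseen outcomes

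*Protocol article*

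**What the plan says.** In the protocol article, Statistical analyses, "the primary analyses use linear mixed-effects models, an approach well suited to handling longitudinal data and missing observations". The closing paragraph of that section repeats the choice, "Missing data are handled through the mixed-model framework, which accommodates incomplete longitudinal data", and then gives the only sensitivity analysis for missing data in the article: "if dropout shows non-random patterns, multiple imputation is applied as a sensitivity check". The section does not define non-random, and it names no imputation variables and no departure from missing at random.

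Under Sample size, "we plan for an upper-bound dropout rate of 20"%, with 36 participants per group. Table 1 schedules PRPSA and STAI at enrolment, T1 and T2 only, so a student who leaves before T1 contributes baseline scores and no later anxiety score. The withdrawal criteria under Participants and recruitment include adverse effects or discomfort, and the Discussion names attrition as a possible limitation.

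**The concern.** A sensitivity analysis is useful when it changes the assumption that is in doubt. A likelihood-based mixed model is valid when dropout depends only on data that the model uses. Ordinary multiple imputation makes the same assumption with respect to the variables in the imputation model. The plan therefore answers a worry about the assumption with a second method that rests on it.

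The trigger has a related weakness, which depends on how it is read:
- **Dropout depends on unseen outcomes.** The observed data cannot show that this has happened, and imputation would not correct it.
- **Dropout depends on observed outcomes or model covariates.** The mixed model already covers this, so imputation adds little.

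At stake is the interpretation of the primary comparison. About 0.20 × 36 = 7 students per arm may lack a T1 score. The outcomes are self-reported, and students know whether they receive VR. Only one arm undergoes VR exposure, so dropout that differs by arm and relates to response is plausible, although the article does not predict it. If the two analyses agreed, a report could present that as robustness when it is weak evidence of it.

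**Working it through.** **1. The plan's own figures.** Inputs from Sample size: d = 0.75 on change scores; "two-tailed independent-measures t-test, α = 0.05, power = 0.80". The noncentral-t calculation gives n = 28.90, so 29 per group (power at 29 = 0.801), as stated. For dropout, 29/0.8 = 36.25, against the stated 36, which leaves 36 × 0.8 = 28.8 per group (power 0.799). The figures are reproduced to within rounding, and nothing below changes them.

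**2. Do the two methods agree?** Simulated trials with T1 missing for dropouts compared two estimates of the T0-to-T1 group difference, in units of the change-score SD. One was the maximum-likelihood mixed-model estimate with unstructured covariance. The other was proper multiple imputation with 20 imputations. There were 1,500 trials at 36 per arm and 60 trials at 2,000 per arm. Assumptions not in the documents are a between-visit correlation of 0.6 and the dropout mechanisms. The true effect was set at -0.75, where negative means a larger reduction with VR.

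| Dropout depends on | Imputation uses | Per arm | Mixed model | Imputation |
|---|---|---|---|---|
| Baseline score | same variables | 36 | -0.743 | -0.743 |
| Unseen T1 change, VR arm | same variables | 36 | -0.987 | -0.987 |
| Unseen T1 change, VR arm | same variables | 2,000 | -0.994 | -0.994 |
| Unseen T1 change, VR arm | plus one auxiliary (r = 0.6) | 36 | -1.006 | -0.973 |
| That auxiliary variable | same variables | 36 | -0.910 | -0.909 |
| That auxiliary variable | plus that auxiliary | 36 | -0.901 | -0.747 |

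In row 2, dropout averaged 12% in the control arm and 26% in the VR arm. Both methods overstate the effect by 0.987 - 0.75 = 0.24. Across trials they correlate at 0.995, with a mean absolute difference of 0.02. With 100 imputations (600 trials) that difference falls to 0.009, so most of it is Monte Carlo noise.

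In row 4 the full-data estimate was -0.757. The mixed-model bias is 1.006 - 0.757 = 0.249, and the auxiliary removes 1.006 - 0.973 = 0.033 of it, about 13%. In row 6 the auxiliary removes essentially all of the bias, because it is what drives dropout there.

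**3. Size, as an illustration only.** Let p be the share of the VR arm that drops out and f the fraction of the VR benefit that those students keep. Assume dropout is otherwise unrelated to outcome, and that the target is the effect in all randomised students. Then

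true effect = 0.75 × [1 - p(1 - f)], both methods estimate about 0.75, and the overstatement factor = 1/[1 - p(1 - f)].

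| p | f | True effect | Factor |
|---|---|---|---|
| 0.20 | 0 | 0.60 | 1.25 |
| 0.20 | 0.5 | 0.675 | 1.11 |
| 0.15 | 0 | 0.6375 | 1.18 |
| any | 1 | 0.75 | 1.00 |

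The values 0.15 and 0.20 for p are the ends of the attrition range under Sample size; f is assumed. A simulation of p = 0.20, f = 0 (2,000 trials, correlation 0.5) gave 0.594 with full data and 0.742 with each method, a ratio of 0.742/0.594 = 1.25.

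**4. What a delta shift would do.** Worsening the imputed VR-arm values by δ moves the VR mean by p × δ. At p = 0.20, a shift of 0.75 SD moves the estimate by 0.20 × 0.75 = 0.15, from 0.75 to 0.60. This is the f = 0 case reached from the other direction.

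**The case against.** Four points can fairly be made against this.

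- **Agreement is not guaranteed.** A reader might infer that imputation must reproduce the mixed model by construction. The documents do not support that. The trial also records the other anxiety scale, session physiology, and adverse events or discomfort in weeks 1 to 4, and an imputation model could use them. The last row of the first table shows that this can matter. This objection stands, and it limits the point to imputation on the same variables or on weak auxiliaries. Its reach is modest, because the other anxiety scale is measured at the same visits and adds only a baseline value for someone who leaves before T1.
- **The trigger can be read as checkable.** Non-random may mean no more than not completely at random, such as dropout visibly related to arm or baseline severity. That can be examined in the data, so calling the trigger unworkable outright would go too far. Where the relation is to observed outcomes or model covariates, however, the mixed model is already valid.
- **Imputation may serve other analyses.** The change-score tests and General Linear Models are commonly run on complete cases, and imputation could change their results. That also stands, but those analyses are described as complementary to the primary one.
- **Detail may sit in a fuller plan.** The imputation model, and any delta or reference rule, may be set out in a document not shown, and their absence from an article is no fault. The point is narrower: the article itself assigns this method to this trigger, and in its ordinary form the method does not test that departure.

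**Conclusion.** The only stated missing-data check rests, in its ordinary form, on the same assumption as the analysis it is meant to check. With the same variables the two analyses give nearly the same estimate, and under dropout that depends on unseen T1 scores they share nearly the same bias. Auxiliary variables soften this mainly when dropout depends on those recorded data. Agreement between the two would be weak evidence of robustness.

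No particular bias is shown for this trial. A reader might take the factor of 1.25 as an expected overstatement, but it follows directly from assuming that VR dropouts gain nothing beyond control and that the target is all randomised students. The article states neither. If the target were the effect had participants continued, 0.75 would be the right answer in that illustration. The near-agreement on the same variables does not depend on those choices; the size of any bias does. The primary model and the sample size are unaffected.

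**What to change.** In Statistical analyses, say what is meant by non-random dropout. Keep multiple imputation if wished, and name its auxiliary variables. The article describes physiology both as recorded in each session and as collected during VR sessions, so confirm that it exists in both arms before using it.

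Then add one pre-specified analysis for PRPSA and STAI at T1 that departs from missing at random and is run whatever the dropout pattern. Either of these would serve:
- delta-adjusted imputation, worsening the imputed VR-arm values in fixed steps until the conclusion changes, with that tipping point reported; or
- reference-based imputation, with missing VR-arm values imputed from the control arm.

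State which participants and which effect the primary comparison targets, so that the result can be interpreted.

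The cost is a few lines of text and a small amount of extra analysis. Delta shifts can be applied to the imputed datasets in the planned SPSS software. No new data or participants are needed. The downside is a possibly less favourable robustness statement.

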## Discussion

Public speaking anxiety is one of the most prevalent forms of anxiety among students in higher education [30]. Overall, research across countries indicates that public speaking and presentation tasks are among the most anxiety-provoking learning situations in higher education. High proportions of students report significant fear or anxiety in these contexts, and even preliminary evidence suggests that, for some, symptoms can reach clinically meaningful levels [31, 32].

This project attempts to provide university students accessing the UPCS with a safe, controlled, and ecologically valid environment to practice managing PSA in realistic but non-threatening academic contexts, such as exams, research presentations, and oral defenses. Grounded in emotional processing theory [33] and the cognitive-behavioral framework of exposure therapy [34], the intervention leverages a VR-based treatment to elicit anxiety-related responses within a controllable context. This approach allows participants to gradually face and regulate stress while developing adaptive coping mechanisms related to public speaking anxiety. From a scientific standpoint, the project contributes to growing evidence that VR-based interventions can effectively simulate socially evaluative situations, enhancing self-efficacy, emotional regulation, and desensitization processes in individuals with PSA and related forms of performance anxiety [35, 36]. Specifically, the project aims to highlight how the combination of standard counseling with VR-based ERP and ACT-consistent training may enhance therapeutic effectiveness beyond what either approach could achieve alone. By embedding VR-based exposure within an ongoing counseling relationship, the intervention allows feared public speaking situations to be addressed in a graded, controlled, and ecologically valid manner, while simultaneously promoting reflective processing, emotional meaning-making, and values-based through therapist support.

The hypotheses of the study are grounded in the assumption that VR-based interventions and standard counseling exert their effects through partially distinct but complementary mechanisms. Specifically, the VR-ERP components are expected to primarily engage inhibitory learning and habituation processes, facilitating repeated confrontation with feared public speaking situations while preventing avoidance behaviors [37]. This mechanism is hypothesized to result in a reduction of fear, threat expectancy, and perceived cognitive load during performance-related tasks. In parallel, the VR-ACT components, particularly the grounding and mindfulness-based modules, are expected to predominantly influence physiological arousal and somatic tension, fostering greater emotional regulation, acceptance of internal experiences, and present-moment awareness during exposure [38]. The integration of these processes within standard counseling is expected to promote both immediate symptom reduction and durable psychological flexibility, thereby accounting for the persistence of treatment effects observed at follow-up. Together, these findings would support a process-based model in which embodied regulation and experiential exposure jointly contribute to sustained improvements in public speaking anxiety and stress-related outcomes.

The use of real-life–like VR scenarios enables repeated exposure to socially evaluative contexts that closely approximate everyday academic demands, such as oral presentations and audience scrutiny, thereby strengthening generalization to real-world functioning [39, 40]. Moreover, the integration of ACT-based VR exercises provides a complementary mechanism by fostering acceptance of internal experiences, cognitive defusion, and present-moment awareness during exposure, rather than focusing exclusively on symptom reduction [41]. From a technological perspective, the project fosters innovation in human–machine interaction and the use of real-time biofeedback to support mindfulness and stress regulation. Future developments could incorporate artificial intelligence–driven adaptive content to personalize exposure intensity and virtual instructor feedback, increasing ecological validity and therapeutic responsiveness. The integration of quantitative (psychophysiological and psychometric) and qualitative (subjective experience) data will provide a comprehensive understanding of VR’s impact on anxiety management and user engagement.

This study has the potential to help address factors associated with university dropout rates linked to anxiety, contribute to improvements in overall psychological well-being among university students, and offer an accessible, and potentially cost-effective alternative to traditional psychotherapy. Additionally, the project strengthens interdisciplinary collaboration between psychology, engineering, and computer science students, fostering professional competencies in digital mental health design.

Some potential limitations and practical challenges may arise during the implementation of this study. One limitation of this study is its requirement for high participant commitment, which may have reduced engagement and increased attrition, thereby limiting the generalizability of the findings. Another limitation concerns the sample composition, as the study focuses on help-seeking university students, a group that may differ in motivation, access to technology, and psychological awareness compared to the general population or younger adolescents. This restricts the ability to generalize the results to other demographic or clinical groups. Finally, the relatively short follow-up period restricts conclusions regarding the long-term maintenance and generalization of treatment gains to real-world academic performance contexts.

Despite these constraints, the study is expected to provide valuable preliminary evidence regarding the feasibility, acceptability, and potential efficacy of VR-based interventions for anxiety management within higher education. The results will help inform the design of larger randomized controlled trials and support the development of scalable, evidence-based digital interventions that integrate VR with established therapeutic approaches, with the aim of enhancing accessibility, engagement, and personalization in mental health care.

## Data Availability

No datasets were generated or analysed during the current study.

## Abbreviations

ACT: Acceptance and Commitment Therapy
BVP: Blood Volume Pulse
CBT: Cognitive Behavioral Therapy
EDA: Electrodermal Activity
ERP: Exposure and Response Prevention
HMD: Head-mounted Display
HR: Heart Rate
HRV: Heart Rate Variability
IBI: Inter-Beat Interval
IVR: Immersive Virtual Reality
PPG: Photoplethysmography
PRPSA: Personal Report of Public Speaking Anxiety
PSA: Public Speaking Anxiety
RCT: Randomized Controlled Trial
STAI: State-Trait Anxiety Inventory
UPCS: University Psychological Counseling Service
VR: Virtual Reality
VRET: Virtual Reality Exposure Therapy
